### Secondary Objective

In accordance with the Fifth National Mental Health and Suicide Prevention Plan [9], the secondary objective of this clinical trial is to reduce the rate of suicidal thoughts and/or behaviors by promoting access to comprehensive services and reducing barriers to care, as well as improving service quality and evidence-based clinical interventions. It is hypothesized that use of the platform within traditional mental health services will facilitate earlier identification and rapid service response (eg, earlier appointment with a health professional) to high levels of suicidal thoughts and/or behaviors.

InnoWell Platform functionality.Multidimensional assessment across a range of domains (eg, sleep, anxiety, mood, physical health)Suicidal thoughts and/or behaviors and at-risk mental state identification and subsequent escalation to required interventionDashboard of results across the range of biopsychosocial domainsAlgorithms to determine severity of needs across these biopsychosocial domainsAlgorithms to allocate clinical stage and suggested levels of careReal-time data tracking and interactive progress reportShared care planning between treating health professional and consumerVideo-visit with a health professionalSupport person input and health information sharingCoordination of care across multi-disciplinary servicesAggregate service performance indicator dashboard

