## Methods

### Study Design

This paper employs a naturalistic prospective clinical trial design wherein all consumers presenting for care to a service utilizing the InnoWell Platform as part of their standard clinical care will be offered the opportunity to use the platform.

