#### Secondary Outcome

Service-level performance data regarding improvements in safety and clinical quality will be derived from the platform, with an emphasis on identification and rapid response to consumers endorsing suicidal thoughts and/or behaviors (see Figure 4). Outcomes will include the percentage of consumers endorsing suicidal thoughts and/or behaviors across 4 severity levels (ie, none, low, medium, and high) at service entry, the number of suicide escalations (ie, notifications to health professionals) for a specific period and during an entire episode of care, and time between suicide escalation and an action by a health professional (eg, call to consumer, schedule follow-up appointment, and contact emergency services).

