### Data Analysis

Scientific validity will be evaluated using interrater reliability statistical methods, such as Cohen kappa coefficient, to quantify the degree of agreement within and among the 4 ratings of stage-based stepped care (ie, platform-generated, health professional allocated, in-service multidisciplinary consensus, and independent expert-clinician reference group). The clinical performance, including aspects of safety, of the platform will be evaluated using aggregate data derived from clinical rating scales completed by the consumer and health professional to measure and track health domain intensity, frequency, quality, and change over time, and aggregate service-level performance data, including safety and clinical quality (eg, time to first assessment, service accessibility, wait time for clinical intervention, service efficiency, and user satisfaction). Within- and between-group analyses using multivariate statistics (eg, multivariate analyses of variance, Kruskal-Wallis test) will be computed to evaluate differences in clinical outcomes among services and among population groups. In addition, reliable change and effect-size scores will be calculated to determine clinical improvement over time for consumer data and then aggregated for service-level outcome data. Analytical validity will be assessed using trends only (ie, descriptive statistics) as a means to determine user engagement and overall effectiveness of the technical performance of the platform.

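### The secondary objective claims fewer suicidal thoughts and behaviors and an earlier response, but the listed secondary outcomes can only describe these under the platform, not show an effect of it

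*Protocol article*

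**What the plan says.** Under Secondary Objective the article states that "the secondary objective of this clinical trial is to reduce the rate of suicidal thoughts and/or behaviors". The hypothesis attached to it is that the platform will "facilitate earlier identification and rapid service response (eg, earlier appointment with a health professional) to high levels of suicidal thoughts and/or behaviors". The Conclusions of the Abstract repeat the reduction aim and extend it to suicide itself.

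Under Secondary Outcome three measures are listed:

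1. "the percentage of consumers endorsing suicidal thoughts and/or behaviors across 4 severity levels (ie, none, low, medium, and high) at service entry"
2. "the number of suicide escalations (ie, notifications to health professionals) for a specific period and during an entire episode of care"
3. "time between suicide escalation and an action by a health professional"

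That section presents them as performance data on improvements in safety and quality. Study Design describes one naturalistic cohort in which "all consumers presenting for care to a service utilizing the InnoWell Platform as part of their standard clinical care will be offered" access to it. Data Analysis adds, for clinical outcomes in general, that "reliable change and effect-size scores will be calculated to determine clinical improvement over time for consumer data", and plans comparisons among services and population groups.

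**The concern.** The objective and hypothesis are worded as effects: a lower rate, and an earlier response. An effect needs an outcome that can move in a known direction and a reference to compare it with. For the reduction, the listed outcomes supply neither. For response speed there is an outcome but no reference.

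At stake is the reading of the results. A rise in escalations could be presented as better identification, and a fall as less suicidality, so either could be called success. A claim that a digital platform reduces suicidal thoughts or behaviors would carry weight with services and funders, and the data as specified could not support or refute it.

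**Working it through.** The article states no rate, effect size, power or follow-up length for this objective, so there is no figure to reproduce. The check sets objective, outcomes, design and analysis side by side.

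**1. What each claim needs.** A reduction needs suicidality measured after the platform could have acted, and a reference for what it would otherwise have been. *Earlier* needs a time measured the same way with and without the platform.

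**2. Severity at entry.** This is one measurement at the start of care. It cannot show change within a consumer. Entry percentages from successive periods could be compared, but they would reflect who presents. The case mix will also shift as centers join: Trial Site and Participating Centers lists five youth services and one veterans' service, with other types possible later.

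**3. Number of escalations.** Write the expected count, ignoring false alarms, as

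E = N × m × p × s

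where N is the number of consumers, m the completed suicidality surveys per consumer, p the true proportion at the notification level, and s the share of those that the platform flags.

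- N has no limit (Sample Size).
- m is not fixed, because participants use the platform of their own accord (Participant Procedures).
- s can change, because measures, thresholds and algorithms may be tailored and revised (Configuration; Ongoing Development of Functionality).
- The objective predicts that p falls. The identification hypothesis predicts that s rises. These move E in opposite directions.

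Dividing by completed surveys gives E / (N × m) = p × s. That removes the dependence on enrolment and survey frequency. It still does not separate p from s, so a denominator makes the count readable but does not turn it into evidence of a reduction.

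**4. Time from escalation to action.** This outcome fits the response part of the hypothesis. Its clock starts when the platform sends a notification, so as defined it has no equivalent in care without the platform. The result is a level of response time, not a gain.

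**5. Possible references.**

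- Consumers who opt out have read-only access and enter no new data (Opt Out Process).
- The services and population groups compared under Data Analysis all use the platform.
- No section names a service without the platform, a period before launch, or a historical series.

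**6. Change scores under Data Analysis.** Suicidality is among the assessed domains (Participant Procedures) and the core domains (Configuration), so these scores could cover it. They are generic, are not linked to the secondary objective, and have no control. Change in consumers who present when unwell mixes any platform effect with regression to the mean, usual care and selective completion of later surveys. As an illustration only, with assumed inputs on a continuous score, a consumer 1.5 SD above the mean at entry is expected to fall by (1 − r) × 1.5 SD with no effect at all:

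- r = 0.5: 0.5 × 1.5 = 0.75 SD
- r = 0.7: 0.3 × 1.5 = 0.45 SD
- r = 0.8: 0.2 × 1.5 = 0.30 SD

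**The case against.** The strongest defense is that the reduction is an aim borrowed from a national plan, while the hypothesis that the study actually states concerns identification and response. On that reading the outcomes fit well: entry severity and escalations describe identification, and time to action describes response. Performance can also be compared across periods and across services, which gives *improvements* some meaning within the platform. How the data would be presented cannot be judged in full, because the figure cited for them is not shown.

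Much of this stands, and it limits the point. A reader might infer that nothing follows suicidality after entry. That is not so: escalations are counted across the whole episode, and a notification marks high suicidality, if imperfectly. A reader might infer that no analysis of change is planned. That is not so either, since the reliable-change and effect-size scores can include suicidality. Nor is it right to say that response speed goes unmeasured. It has its own outcome and lacks only a reference.

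What does not stand is that these features answer the objective as worded. The text calls the reduction an objective of this trial, and the hypothesis itself says *earlier*. Comparisons within the platform do not isolate its effect. Nor is this detail that an unseen analysis plan would ordinarily supply: the mismatch lies between statements that the article makes, and an analysis plan cannot add a comparator to the design.

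**Conclusion.** The concern holds in a limited form. For the reduction, the listed secondary outcomes include no measure of change in the rate, and there is no reference. For response speed, the outcome exists and only the reference is missing. The change scores under Data Analysis narrow the first gap but do not close it, because they are neither assigned to this objective nor controlled.

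The size is qualitative. The standard-deviation figures above rest on an assumed starting point and assumed correlations, on a continuous scale rather than the four-level category, and for an analysis that is not a listed outcome. They show why the caveat is needed and should not be read as the size of the defect.

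A reader might go further and infer that the trial as a whole is undermined. The document does not support that: the primary objective, agreement among four ratings of clinical stage, does not depend on any of this. The correction should be made, but it is not one on which the main result turns. The conclusion assumes that no reference without the platform exists in a fuller protocol; none is mentioned in the article.

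**What to change.** - **Reword the objective and hypothesis as descriptive**, for example: *to describe the identification of, and service response to, suicidal thoughts and behaviors among consumers using the platform*. State that a reduction, an earlier response or an improvement will not be concluded as an effect of the platform. Align the Conclusions of the Abstract.
- **Name one further secondary outcome:** change in the four-level suicidality category from entry to later completed surveys, shown as a transition table by entry level. State the caveats with it: regression to the mean, usual care, and selective survey completion.
- **Give escalations a denominator:** per consumer or per completed suicidality survey, alongside the raw count.
- **Label any wait-time comparison by entry suicidality** (high versus lower) as a description of triage only. It says nothing about care without the platform.
- **Optional:** a comparison of wait time before and after a service's own go-live, only where that service already holds such records. The article does not say that any does, so the plan should not rely on it.

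The core changes are rewording, one further table and a denominator, all from data that the platform already collects. The downside is a more modest secondary claim.

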## Methods

### Study Design

This paper employs a naturalistic prospective clinical trial design wherein all consumers presenting for care to a service utilizing the InnoWell Platform as part of their standard clinical care will be offered the opportunity to use the platform.

### Trial Site and Participating Centers

The InnoWell Platform is a Web-based app, and all data are collected electronically. As the sponsor and locality of the research team, the University of Sydney is considered the physical trial site. At the time of this publication, participants were being recruited from the following participating centers: headspace services (Camperdown, Coffs Harbour, Lismore, and Port Macquarie in New South Wales, and Edinburgh North in South Australia) and Open Arms—Veterans and Families Counselling in Surry Hills, New South Wales. Future participating centers may include services for children and their families, adult staged-care services, older persons mental health, general practice, as well as Aboriginal and Torres Strait Islander designed and controlled services.

### Participants

#### Eligibility Criteria

All consumers aged 2 years and older presenting for care to a traditional face-to-face or Web-based mental health service utilizing the platform as part of their standard clinical care will be eligible to participate in the clinical trial. This will include persons from the following populations: children and their families, young people, adults, older adults, the Veteran community, Aboriginal and Torres Strait Islander peoples, people from culturally and linguistically diverse backgrounds, the lesbian, gay, bisexual, transgender, and intersex community, and those from broader education and workforce sectors, as well as persons with disabilities, lived experience of comorbidity (including alcohol or other substance misuse), complex disorders, and/or suicidality. Owing to the nature of its research design, this clinical trial does not have defined exclusion criteria.

#### Sample Size

The clinical trial does not have an upper or lower limit on the number of participants.

#### Screening Procedures

It will be standard clinical care for all consumers presenting to a traditional face-to-face or Web-based mental health service utilizing the InnoWell Platform to be directed to the platform for assistance in assessment, management, and monitoring of their mental ill health and maintenance of well-being.

On contacting the service either by telephone (or short message service), on the Web (eg, email, chat), or in person, the consumer will be introduced to the clinical trial via an ethics-approved script. Although this script is generic and adaptable to different populations, settings, and services, it informs the consumer of what is involved in using the platform and notifies them that the data collected by the platform will be shared with their service provider to promote person-centered collaborative care and shared decision making. If the consumer is interested and responds “Yes,” they will receive a unique email invitation to sign up to the platform. When the participants receive the email invitation, they will be required to accept the invitation and be directed to “Sign up” by creating an account. If they do not sign up immediately, they will be sent a reminder via short message service. The participants will be required to review and accept both the “Privacy” and “Terms of use” within the platform before proceeding to a “Research data sharing” screen, which is where details about this clinical trial are contained.

#### Informed Consent

##### Opt Out Process

As part of the standard “Terms of use” of the platform, participants aged 14 years and older will be informed that their deidentified health data collected by the platform will be used for research purposes unless they “opt out.” If participants decide to “opt out,” they can indicate this by ticking a box. This action will be noted in the platform’s database, and it will automatically switch their access to the platform to read only, preventing them from entering any new data. If participants do not “opt out,” their deidentified data will be accessible by members of the research team. Importantly, participants will be able to edit their data sharing permissions at any time, such that any future data collected about them will not be accessible to researchers if, for example, they choose to withdraw from the clinical trial. The “opt out” consent approach described above is an efficient procedure without violating the option of providing choice. The approach taken considers a participant’s willingness rather than refusal to participate in the clinical trial and provides the necessary information to make an informed decision. Finally, the risk to the participants can be considered very low, as their data are deidentified (ie, all personal identifiers removed, including name, date of birth, and email address).

##### Parental Consent Requirements and Process

For children between the ages of 2 and 11 years, consent for the deidentified data to be used for research purposes will be provided solely by the parents/guardians. Child assent will not be sought. The parents/guardians will also serve as the “consumer” in these instances, answering the surveys in relation to the child. For consumers aged 12 and 13 years, parents/guardians will again be required to provide consent for the young person’s deidentified data to be used for research purposes. In addition, as per the standard process described above, the young person will be given the option to “opt out” of sharing his or her data through the standard “Terms of use” provided when participants access the platform. For deidentified data to be used for research purposes, both parents/guardians and the young person (if aged 12 or 13 years) need to have provided permission to do so (ie, if the parent consents but the young person “opts out,” the data will not be used and vice versa). Parents/guardians of children aged 13 years or younger will receive a standard introduction email to the platform sent by the service, which will include brief information regarding the research, as well as a link to further details, and a page where parents/guardians can indicate consent (or not) for the use of their young person’s data for research purposes. This parental consent is specifically related to the storage and use of their young person’s data for this clinical trial. Thus, if a parent/guardian chooses not to consent to the use of data for this clinical trial, there will be no impact on the young person’s standard clinical care; however, their access to the platform will be automatically switched to read only.

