### The InnoWell Platform

Through a process of participatory design with lived experience, health professionals, and service staff (including administration and management), we have developed a Web-based platform (the InnoWell Platform) that supports the prevention, early intervention, treatment, and continuous monitoring of mental ill health and maintenance of well-being in people aged 2 years and older [20]. The platform is a customizable digital tool kit that operates through existing service providers who utilize the system to provide their consumers with access to evidence-based assessments and feedback, intervention options, and outcome monitoring. It does this by collecting, storing, and reporting personal and health information back to consumers and their health professionals to promote collaborative care partnerships that aim to improve the management of mental ill health and maintenance of well-being. This platform uses multiple sources of information to develop a comprehensive understanding of the consumers’ needs and track their progress over time. This primarily involves Web-based self-reported psychometric measures from both consumers and their health professionals, as well as objective behavioral data collected via third-party integrations. Textbox 2 highlights the functionality built into the InnoWell Platform.

Specifically, in relation to suicide prevention, the InnoWell Platform employs a suicide escalation protocol derived from previous work [18]. In the current platform, suicidal thoughts and/or behaviors are assessed using 2 self-report surveys: Suicidal Ideation Attributes Scale [21] and Columbia-Suicide Severity Rating Scale [22]. Suicidal ideation without plan or intent in the past month triggers a pop-up for the consumer in the platform, providing details for crisis support services. Self-report of suicidal ideation with a plan and/or intent and/or a suicide attempt within the past 3 months triggers both the pop-up for the consumer and sends a notification to the consumer’s health professional, requiring a clinical care action (eg, telephone contact, action safety plan).

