Given the emphasis on suicide prevention, the InnoWell Platform has been built to include immediate access to crisis support options. At any time when engaging with the platform, a participant has access to the “I need help now” button (see Figure 3), which provides contact details for crisis services (eg, Lifeline, Beyond Blue, and Kids Helpline). As described previously, these support options also appear as a pop-up directly after the participant scores low, moderate, or high on the suicidal thoughts and/or behaviors health card. When a participant scores high on this health card, a notification of suicide risk is also triggered for the treating health professional requiring clinical action.

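### Parental refusal of research use is said not to affect standard care, yet it makes the platform read only and so removes survey-triggered suicide escalation

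*Protocol article*

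**What the plan says.** Research use can be refused in two ways. Participants aged 14 and older may tick an opt-out box, and under Opt Out Process "it will automatically switch their access to the platform to read only, preventing them from entering any new data". For children aged 13 or younger a parent or guardian must consent; those aged 12 and 13 also have their own opt-out by the standard process. If the parent declines, the consequence given under Parental Consent Requirements and Process is "no impact on the young person’s standard clinical care; however, their access to the platform will be automatically switched to read only". That section also limits this consent to storage and use of the data for the trial.

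On suicide safety, The InnoWell Platform section says that "suicidal thoughts and/or behaviors are assessed using 2 self-report surveys". Ideation without plan or intent in the past month brings up crisis contacts for the consumer. For a plan or intent, or an attempt in the last 3 months, the response is stronger: it "triggers both the pop-up for the consumer and sends a notification to the consumer’s health professional, requiring a clinical care action". Participant Procedures repeats this in terms of the health card: crisis contacts "appear as a pop-up directly after the participant scores low, moderate, or high", and on a high score "a notification of suicide risk is also triggered for the treating health professional requiring clinical action".

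Screening Procedures describes directing consumers to the platform as standard clinical care. Participant Procedures says the same of completing the surveys.

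**The concern.** A parent reading the assurance would take it that refusing research leaves the child's care as it was. If the platform surveys belong to that care, and refusal stops them, the assurance is untrue. What stops includes the mechanism by which the platform detects suicidal thoughts and alerts a clinician. The Secondary Objective hypothesizes that platform use brings earlier identification of, and faster response to, high suicidality. A permission that concerns only research data would then decide whether a consumer who wants to use the platform has a safety-relevant clinical function, and the parental consent text would say that nothing changes.

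**Working it through.** There is no figure to reproduce; the check is whether the statements can all be true together.

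1. **Refusal leads to read only.** This is stated for self opt-out (Opt Out Process) and for parental refusal (Parental Consent Requirements and Process).
2. **Read only means no new entries.** This is spelled out in Opt Out Process: "it will automatically switch their access to the platform to read only, preventing them from entering any new data". The parental section uses the same term without defining it again. I assume the same meaning, which is the natural reading.
3. **No new entries means no new suicidality score.** The platform measures suicidality by self-report survey, and Participant Procedures says that completed surveys populate the health cards. For children aged 2 to 11 the parent answers the surveys, so the block falls on the parent's entries.
4. **No new score means no new survey-triggered escalation.** The pop-up follows a low, moderate or high score, and the clinician notification follows a high score. Without a new score neither can occur. The article describes no other way for refusers to complete the surveys.
5. **The surveys are part of standard care.** Screening Procedures and Participant Procedures say so, and Study Design and The InnoWell Platform Description also place the platform within standard clinical care.
6. **The assurance.** Steps 1 to 5 mean that parental refusal removes something the article counts as standard care. The statement that standard care is unaffected cannot stand beside them.

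The refusal routes compare as follows:

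| Route | Survey entry and survey-triggered escalation lost | Standard care said to be unaffected |
|---|---|---|
| Own opt-out, 14 and older | Yes | No |
| Own opt-out, 12 to 13 (standard process) | Yes | No |
| Parental refusal, 13 or younger | Yes | Yes |

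The functional loss is common to all three routes; the contradiction belongs only to the third.

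Two conditions limit the loss. Participant Procedures and Configuration leave the surveys to each service, and suicidality is a core domain that services are encouraged, not required, to assess. The loss therefore arises only where those surveys are configured. It also concerns only what a survey score triggers: Primary Outcome describes clinician assessment within standard care, and Participant Procedures describes a crisis help button that is not tied to survey entry. Neither is stated to stop.

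**The case against.** The best defense is that the sentence discloses the restriction itself: after its "however"-type turn the reader learns that access becomes read only. One can read it as saying that care from the service continues while platform access is limited. Use of the platform is voluntary, and a consumer who never signs up also has no survey-triggered escalation and still receives care. This shows that the loss is bounded. It does not rescue the sentence, because the article itself places the surveys inside standard care, and because disclosing read only does not tell a parent that escalation goes with it.

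It is also fair that the terms of use, the parent email and its linked details are not shown. They may already explain the loss, so the point concerns the article's text and what those materials need to say.

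Four stronger readings are tempting, and the document does not support them:

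- A reader might infer that refusers lose all suicide-risk care. Only the survey-triggered part is shown to be lost.
- A reader might infer that the protocol contradicts itself for those aged 14 and older too. It does not: Opt Out Process states the consequence and makes no contrary promise. Objecting to the switch there is a disagreement with a disclosed design choice.
- A reader might infer that the statement of very low participant risk in Opt Out Process is refuted. That statement concerns research use of deidentified data, not the position of those who decline.
- A reader might infer that young children are being affected now. The six current centers are five youth services and one veterans' service, with no age ranges given, and services for children and families are named only as possible future centers.

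**Conclusion.** The point holds for parental refusal: the assurance conflicts with the article's own account of standard care, and the conflict touches a safety function. For self opt-out the same function is lost without a contradiction. The size cannot be expressed as a number of people, because the article gives no refusal rate, no age distribution at current centers and no list of which services configured the suicidality surveys. For any affected user the effect is complete within its scope: no new survey-triggered pop-up or notification while access is read only. The conclusion assumes that read only means the same in both consent sections and that the suicidality surveys are configured. It does not extend to people who later edit their data-sharing permission, since that edit is not itself stated to trigger read only. The correction should be made because the wording is wrong, the subject is safety and the minimum remedy is cheap.

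**What to change.** **Minimum.** In Parental Consent Requirements and Process, delete or qualify the assurance. State in the parent email and the terms of use that refusing research use removes survey entry and, with it, survey-triggered suicide escalation, so that suicide risk for refusers is assessed by the clinician in usual care. This costs wording and an ethics notification.

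**Preferred, if the platform allows it.** Remove the read-only switch and let the data-sharing permission and the parental consent govern only what enters the research extract. Refusers would then keep survey entry and escalation. Opt Out Process already contemplates such a permission for participants who change their settings later: "any future data collected about them will not be accessible to researchers". The cost is a platform configuration change, for which the article gives no figure, plus consent and protocol wording and an ethics notification. The downside is that opt-outs may rise once refusal no longer costs survey entry, which could change the research sample and leave some entered data unavailable to the researchers.
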